## Abstract

**Background:**

Intraoperative hypotension is common in patients having non-cardiac surgery and is associated with serious complications and death. However, optimal intraoperative blood pressures for individual patients remain unknown. We therefore aim to test the hypothesis that personalized perioperative blood pressure management—based on preoperative automated blood pressure monitoring—reduces the incidence of a composite outcome of acute kidney injury, acute myocardial injury, non-fatal cardiac arrest, and death within 7 days after surgery compared to routine blood pressure management in high-risk patients having major abdominal surgery.

**Methods:**

IMPROVE-multi is a multicenter randomized trial in 1272 high-risk patients having elective major abdominal surgery that we plan to conduct at 16 German university medical centers. Preoperative automated blood pressure monitoring using upper arm cuff oscillometry will be performed in all patients for one night to obtain the mean of the nighttime mean arterial pressures. Patients will then be randomized either to personalized blood pressure management or to routine blood pressure management. In patients assigned to personalized management, intraoperative mean arterial pressure will be maintained at least at the mean of the nighttime mean arterial pressures. In patients assigned to routine management, intraoperative blood pressure will be managed per routine. The primary outcome will be a composite of acute kidney injury, acute myocardial injury, non-fatal cardiac arrest, and death within 7 days after surgery.

**Discussion:**

Our trial will determine whether personalized perioperative blood pressure management reduces the incidence of major postoperative complications and death within 7 days after surgery compared to routine blood pressure management in high-risk patients having major abdominal surgery.

**Trial registration:**

ClinicalTrials.gov NCT05416944. Registered on June 14, 2022.

**Supplementary Information:**

The online version contains supplementary material available at 10.1186/s13063-022-06854-0.

## Background

About 2% of patients having inpatient non-cardiac surgery die within the first month after surgery in Europe [1] and the USA [2]. If the first month after surgery would be considered a disease, it would be the third leading cause of death worldwide [3]. Postoperative deaths are a consequence of postoperative complications—including acute kidney injury and acute myocardial injury [2]. To improve postoperative outcomes, modifiable risk factors for complications should be identified and addressed. One of these modifiable risk factors may be intraoperative hypotension.

Intraoperative hypotension is common in patients having non-cardiac surgery and is associated with serious complications—such as postoperative acute kidney and myocardial injury [4–6]—and even death [6, 7]. The association between intraoperative hypotension and serious complications is supported by many observational database studies [8]—but the extent to which the relation is causal remains unclear.

Optimal intraoperative blood pressures for individual patients also remain unknown. On a population basis, intraoperative mean arterial pressures less than 60–70 mmHg are associated with organ injury [4, 5, 9], leading to the recommendation that intraoperative mean arterial pressures should generally be kept above 65 mmHg [10, 11].

Universally targeting higher intraoperative mean arterial pressures (e.g., 75 mmHg vs. 60 mmHg) does not reduce postoperative complications in patients having major non-cardiac surgery [12]. In contrast, the randomized INPRESS trial suggests that individualized blood pressure management targeting preoperative resting blood pressures reduces postoperative complications compared to routine blood pressure management [13]. However, in the INPRESS trial, individual blood pressure targets were defined based on single preoperative blood pressure measurements which do not adequately reflect individual blood pressure profiles [13–16]. Preoperative automated blood pressure monitoring is thought to be the optimal method to establish baseline values before surgery [17]. We thus propose preoperative automated blood pressure monitoring to define individual intraoperative blood pressure targets.

We aim to test the hypothesis that personalized perioperative blood pressure management—based on preoperative automated blood pressure monitoring—reduces the incidence of a composite outcome of acute kidney injury, acute myocardial injury, non-fatal cardiac arrest, and death within 7 days after surgery compared to routine blood pressure management in high-risk patients having major abdominal surgery.

## Methods/design

### Trial design

The proposed trial will be conducted in accordance with the ethical principles based on the Declaration of Helsinki [18] and the ICH E6 R2 guidelines for good clinical practice. The trial was approved by the ethics committee Hamburg (Ethikkommission der Ärztekammer Hamburg, Hamburg, Germany, registration number 2022–100879-BO-ff) acting as the primary ethics committee for this trial. Secondary ethics committee approvals will be obtained for each trial site before patient recruitment starts. The trial was registered at ClinicalTrials.gov (NCT05416944) on June 14, 2022. This article adheres to the Standard Protocol Items: Recommendations for Interventional Trials (SPIRIT) statement (Additional file 1) [19].

IMPROVE-multi will be a multicenter randomized controlled blinded (participating patients, outcome adjudicators, and data analysts) clinical superiority trial in 1272 high-risk patients having elective major abdominal surgery. We plan to enroll patients at approximately 16 German university medical centers. The trial coordinating center will be the University Medical Center Hamburg-Eppendorf, Hamburg, Germany.

### Patients

We will include consenting patients ≥ 45 years scheduled for elective major abdominal surgery with general anesthesia that is expected to last ≥ 90 min. Patients must fulfill at least one of the following high-risk criteria: exercise tolerance < 4 metabolic equivalents as defined by the guidelines of the American College of Cardiology/American Heart Association; renal impairment (serum creatinine ≥ 1.3 mg/dL or estimated glomerular filtration rate < 90 mL/min/1.73 m^2^ within the last 6 months); coronary artery disease (any stage); chronic heart failure (New York Heart Association Functional Classification ≥ II); valvular heart disease (moderate or severe); history of stroke; peripheral arterial occlusive disease (any stage); chronic obstructive pulmonary disease (any stage) or pulmonary fibrosis (any stage); diabetes mellitus requiring oral hypoglycemic agent or insulin; immunodeficiency due to a disease (e.g., HIV, leukemia, multiple myeloma, solid organ cancer) or therapy (e.g., immunosuppressants, chemotherapy, radiation, steroids [above Cushing threshold]); liver cirrhosis (any Child–Pugh class); body mass index ≥ 30 kg/m^2^; current smoking or 15 pack-year history of smoking; age ≥ 65 years; expected anesthesia duration ≥ 180 min; B-type natriuretic peptide > 80 ng/L or N-terminal B-type natriuretic peptide > 200 ng/L within the last 6 months.

We will not include patients having emergency surgery, nephrectomy, and liver or kidney transplantation; patients who had kidney, liver, heart, or lung transplantation; patients having sepsis (according to current Sepsis-3 definition); pregnant women; and patients in whom preoperative automated blood pressure monitoring is not possible.

### Protocol

The trial flow and measures for each participating patient are provided in Fig. 1 and Table 1.

**Fig. 1 Fig1:**
[figure not shown]
Flowchart illustrating patient screening, enrollment, randomization, trial intervention, and the primary outcome

**Table 1 Tab1:** Frequency and scope of trial visits

	Preoperative	Perioperative	Postoperative						
Day	− *x* to − 1	0	1	2	3	4–6	7	30	90
Visits/contacts	I	II	III	IV	V	VI	VII	VIII	IX
**Informed consent**	X								
**Baseline assessment (i.e., demographic data, medical history)**	X								
**Preoperative automated blood pressure monitoring**	X								
**Blood sampling #1 (baseline values)**	(X)	X							
**Randomization**		X							
**Perioperative blood pressure management**		X							
**Blood sampling #2, 3, 4, and 5**			X	X	X	(X)	X^a^		
**Primary outcome assessment**							X		
**Secondary outcome assessments**					X		X	X	X

^a^If the patient is discharged earlier than day 7, creatinine and high-sensitivity troponin concentrations will be required on the day of hospital discharge

Written informed consent will be obtained by dedicated trial personnel. Baseline demographic and medical characteristics will be recorded and entered in an electronic Case Report Form (eCRF). Preoperative automated blood pressure monitoring will be performed either at home or in the hospital for one night using upper arm cuff oscillometry at 30-min intervals. After excluding artifacts, we will calculate the mean of the nighttime mean arterial pressures. We will define nighttime as 00:00 to 06:00 h [20, 21].

Patients will be randomized in a 1:1 ratio using central block-wise randomization with variable block length stratified by centers with an electronic tool to personalized blood pressure management or to routine blood pressure management. The randomization will be performed directly before the induction of general anesthesia.

In patients assigned to personalized management, intraoperative mean arterial pressure will be maintained at least at the mean of the nighttime mean arterial pressures. If the mean of the nighttime mean arterial pressures will be lower than 65 mmHg, the intraoperative mean arterial pressure will be maintained at least at 65 mmHg; if the mean of the nighttime mean arterial pressures will be higher than 110 mmHg, the intraoperative mean arterial pressure will be maintained only at least at 110 mmHg. The intervention period will start at the induction of general anesthesia and will end 2 h after the end of surgery.

In patients assigned to routine management, intraoperative blood pressure will be managed per routine which usually includes keeping mean arterial pressure ≥ 65 mmHg [5, 10]. Anesthesiologists caring for patients assigned to routine management will not be informed of nighttime blood pressures.

In both groups, the interventions used to achieve the mean arterial pressure target will be at the discretion of treating anesthesiologists and will include intravenous fluid administration, vasoactive medications, adjusting anesthetic depth, and modifying patient position.

In all patients, perioperative blood pressure will be routinely monitored using intraarterial blood pressure monitoring (arterial catheter) or upper arm cuff oscillometry. All other anesthesiologic and surgical procedures will be performed according to routine care and the discretion of the attending anesthesiologists.

### Outcomes

#### Primary outcome

The primary outcome will be a composite of acute kidney injury, acute myocardial injury, non-fatal cardiac arrest, and death within 7 days after surgery.

#### Secondary outcomes

Secondary outcomes will be as follows:Incidence of the composite primary outcome within 3 days after surgery and the incidences of each of the individual components of the primary outcome within 3 and 7 days after surgeryIncidence of a composite outcome of need for renal replacement therapy, myocardial infarction, non-fatal cardiac arrest, and death within 30 and 90 days after surgery and the incidences of each of the individual components of this composite outcome within 30 and 90 days after surgeryIncidence of a composite outcome of infectious complications within 7 days after surgery and the incidences of each of the individual components of this composite outcome within 7 days after surgeryTime-to-event outcome with the event “transfer from intensive care unit to normal ward” within 90 days after surgeryTime-to-event outcome with the event “hospital discharge” within 90 days after surgeryIncidence of unplanned hospital re-admission within 30 days after surgery

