#### Statistical analyses

Descriptive analysis will be performed to describe the patient characteristics and clinical data. The primary and secondary outcomes will be analyzed according to the intention-to-treat principle. The primary outcome analyses (interim as well as final analysis) will be conducted using a two-sided test of proportions with continuity correction. When a total of 636 patients will have been observed for 7 days, an unblinded interim analysis will be performed. If the resulting *p*-value is < 0.0015 one-sided, the null hypothesis will be rejected, and the trial will be stopped for efficacy. Otherwise, recruitment will be continued. At the end of the trial, the statistical test for the primary outcome will be performed at a significance level of 0.049 two-sided.

In secondary outcome analyses, the incidence of each of the individual components of the primary outcome and of the additional secondary outcomes will be analyzed using a two-sided test of proportions with continuity correction. In additional analyses, the primary outcome and its individual components will be treated as time-to-event outcomes. Due to the competing event death, all time-to-event outcomes will be assessed using Aalen-Johansen estimators and accompanied by effect estimates based on cause-specific Cox regressions. In further analyses, the primary and secondary outcome analyses will be repeated in the per-protocol population. As a sensitivity analysis, the primary outcome will be analyzed using a mixed logistic regression model including a fixed effect for the random group and a random effect for the center to account for the cluster structure in the data. In further sensitivity analyses, regression models (logistic and cause-specific Cox regression) including potential prognostic baseline variables will be used.

If more than 5% of values are missing for the primary outcome, we will use multiple imputation in a sensitivity analysis. The number of imputations for multiple imputation will be chosen depending on the proportion of missing data according to White et al. [28].

A full statistical analysis plan will be developed before any data are evaluated.

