#### Methods against bias

Screening logs will be collected to assess the risk for selection bias in patient recruitment. Randomization codes will be provided by an independent biostatistician to ensure blinding as long as practical. Participating patients, outcome adjudicators, and data analysts will be blinded to group assignment. Furthermore, a blinded outcome committee will be implemented to avoid detection bias. Anesthesiologists treating patients assigned to personalized management cannot be blinded as the results of preoperative automated blood pressure monitoring are necessary for perioperative personalized blood pressure management.

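### The secondary outcome of transfer from intensive care to the ward is possible only for patients admitted to intensive care, and the stated analysis gives never-admitted patients no sensible place

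*Protocol article*

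**What the plan says.** All references are to the Protocol article.

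- **Event (Secondary outcomes).** A time-to-event outcome with a 90-day horizon whose event is "transfer from intensive care unit to normal ward". No time origin is given, and no rule for patients who never enter intensive care.
- **Eligibility (Patients).** "Patients must fulfill at least one of the following high-risk criteria". Intensive-care admission is not among the conditions for entry.
- **Timing (Methods/design, Protocol).** "The randomization will be performed directly before the induction of general anesthesia". Also: "The intervention period will start at the induction of general anesthesia and will end 2 h after the end of surgery".
- **Blinding (Methods against bias).** "Anesthesiologists treating patients assigned to personalized management cannot be blinded".
- **Analysis (Statistical analyses).** "The primary and secondary outcomes will be analyzed according to the intention-to-treat principle". And: "Due to the competing event death, all time-to-event outcomes will be assessed using Aalen-Johansen estimators", accompanied by cause-specific Cox regressions. No competing event other than death is named.

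**The concern.** The event, the population and the estimator do not fit together. The event presupposes an intensive-care stay, the population is everyone randomized, and the estimator treats anyone who has neither died nor been transferred as still waiting for transfer.

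Postoperative admission is settled after randomization. The intervention runs until 2 h after surgery, which overlaps the time when patients are sent to intensive care or to the ward, and anesthesiologists in the personalized arm know the allocation. Admission could therefore differ between arms, in either direction.

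If it does, the result for this outcome mixes two things: how many patients were admitted, and how quickly admitted patients left. A strategy that kept patients out of intensive care, which most readers would call a benefit, could show a hazard ratio below 1 for transfer and be reported as slower recovery.

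**Working it through.** **The plan's own figures.** The article states no admission rate, expected stay or power for this outcome, so there is nothing to reproduce here. The sample size of 1144 does not depend on it.

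**What each handling does with a never-admitted patient**

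- *A. Admitted patients only:* dropped. The comparison is conditional on a status reached after randomization.
- *B. All randomized, event as worded:* never has the event and stays in the risk set to day 90, like a patient who never left intensive care. Without deaths, the Aalen-Johansen curve levels off at the share admitted, so the arm with more admissions has the higher, seemingly better, curve.
- *C. All randomized, zero intensive-care days:* counted, with the best value.

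**Illustration (all inputs assumed).** Severity s is uniform on 0 to 1. An arm with admission share π admits its sickest patients, s > 1 − π. Patients leave intensive care at rate 2e^(−2s) per day, so the mean stay at severity s is ½e^(2s) days. There are no deaths, and treatment has no effect on stay at a given severity. The arms differ only in π, and the avoided admissions are the less severe, shorter stays. Subscripts: 0 routine, 1 personalized.

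Intensive-care days per randomized patient:
M(π) = ∫ ½e^(2s) ds from 1 − π to 1 = ¼(e² − e^(2(1−π))).

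- M(0.30) = ¼(7.389 − 4.055) = 0.833; M(0.25) = ¼(7.389 − 4.482) = 0.727
- M(0.50) = ¼(7.389 − 2.718) = 1.168; M(0.40) = ¼(7.389 − 3.320) = 1.017
- M(0.90) = ¼(7.389 − 1.221) = 1.542; M(0.85) = ¼(7.389 − 1.350) = 1.510

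*Handling A.* Transfer-rate ratio, personalized to routine = [M(π₀)/π₀] / [M(π₁)/π₁]:

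- 30% vs 25%: 2.778/2.907 = 0.96
- 50% vs 40%: 2.335/2.543 = 0.92
- 90% vs 85%: 1.713/1.776 = 0.96

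*Handling B, crude.* Events per person-day = π / [M(π) + 90(1 − π)]:

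- 30% vs 25%: 0.25/68.227 against 0.30/63.833, ratio 0.78
- 50% vs 40%: 0.40/55.017 against 0.50/46.168, ratio 0.67
- 90% vs 85%: 0.85/15.010 against 0.90/10.542, ratio 0.66 (a simulation of the same model gave 0.67, within its sampling error)

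*Handling B, as Cox would see it.* The crude ratio spreads person-time over 90 days, although nearly all transfers come early, so it is not the planned hazard ratio. The large-sample Cox ratio θ solves ∫[f₁ − (f₀ + f₁)θY₁/(θY₁ + Y₀)]dt = 0. Here f is the density of transfers per randomized patient, and Y is 1 − π plus the share still in intensive care. Solved numerically, θ is 0.805, 0.733 and 0.855.

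| Admission, routine vs personalized | A: rate ratio | B: crude ratio | B: Cox ratio | C: mean intensive-care days, routine vs personalized |
|---|---|---|---|---|
| 30% vs 30% | 1.00 | 1.00 | 1.00 | 0.83 vs 0.83 |
| 30% vs 25% | 0.96 | 0.78 | 0.805 | 0.83 vs 0.73 |
| 50% vs 40% | 0.92 | 0.67 | 0.733 | 1.17 vs 1.02 |
| 90% vs 85% | 0.96 | 0.66 | 0.855 | 1.54 vs 1.51 |

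In the last three rows the personalized arm uses fewer intensive-care days. A and B both put it at a disadvantage, and C gives the correct direction. With equal admission there is no distortion.

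**The case against.** The strongest reply is that the outcome is a one-line label in a condensed article. Time origin, risk set and conventions are normally set in the statistical analysis plan, which the article promises before any data are evaluated. That plan could give never-admitted patients the event at time zero, or zero intensive-care days. This stands in part. A reader might infer that the outcome must either break randomization or score the best patients as failures. The article does not support that, because it excludes neither convention. The point is nevertheless more than missing detail: the article already fixes the event, the population and the estimator, and a patient never in intensive care has no transfer to record. A time-zero rule would redefine the event, which is the repair sought here.

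A reader might also conclude that the intention-to-treat statement is false for this outcome. It would fail only if the analysis were restricted to admitted patients, which the article does not say. If everyone is kept, intention to treat holds and the problem is the scoring.

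The size and direction are also open to challenge, and this objection stands. No admission rate is given. If admission is routine or planned before surgery, the arms may hardly differ. Treating to an individual pressure target could raise admission rather than lower it, and the distortion would then favour the personalized arm.

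Two further criticisms are tempting but should not be made. Not counting a return to intensive care is normal for a first-event outcome. Unplanned re-admission that leaves out death is a matter of preference, since death within 30 days is itself reported.

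**Conclusion.** The point holds, with limits. As worded, the outcome is defined only for patients who reach intensive care, while the stated analysis covers everyone randomized. The two handlings closest to the text are no event, or exclusion. Each can work against the arm with fewer admissions; for exclusion this also assumes that the avoided stays are the shorter ones.

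The size cannot be derived from the article. In the assumed scenarios, exclusion gives a modest distortion (ratio 0.92 to 0.96) and the literal reading a larger one (Cox ratio about 0.73 to 0.86). Both vanish when admission rates are equal. These figures show direction and possible size and are not estimates for this trial. They do not support the inference that the trial is biased against personalized management.

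Only a secondary outcome is affected. The primary outcome, sample size and interim boundary are untouched. The change is worth making because the flaw could reverse the apparent direction of a prespecified result and is cheap to remove.

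**What to change.** Define the outcome for all randomized patients, in one of two ways:

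1. **Days alive and outside intensive care to day 90.** Never-admitted patients have zero intensive-care days and repeat stays are added. State in advance how death before day 90 is scored. Because randomization is stratified by center, a center-stratified rank test is a natural comparison.
2. **If time-to-event is kept:** time from the end of surgery to being alive and out of intensive care, with never-admitted patients having the event at time zero and death competing. This keeps the planned Aalen-Johansen and Cox framework. Check that the software retains events at time zero.

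Under either option, report intensive-care admission by arm.

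**Cost.** The outcome wording and a paragraph in the analysis plan, which the article says is still to be written. Intensive-care admission and discharge dates are needed, including repeat stays for option 1; medical records are already a data source. The trial is registered, so replacing the outcome rather than clarifying it may call for a registry update. Option 1 has a small downside: it mixes mortality with length of stay, so deaths and intensive-care days should be reported separately as well.
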